## Discussion

We presented a protocol for assessing the cost-effectiveness of our home-based educational programme and its generalisability. The implementation of the educational programme might both benefit patients and society.

*Cost-effectiveness:* If indeed our hypotheses are confirmed, and the home-based educational programme is cost-effective, then there are convincing arguments to make the programme standard care in the Netherlands. Health insurers already expressed their interest in the programme; this implementation study is supported by *Zorgverzekeraars Nederland* (the Netherlands Health Insurers), which is the ‘umbrella organization’ of all health insurers in the Netherlands. Additionally, the Dutch Kidney Foundation supports the programme and contributed through three grants in the developmental phases of the home-based educational programme. The Dutch Kidney Foundation is a non-profit organisation which subsidises research and innovation in nephrology and renal transplantation care. Indeed, the health insurance companies have good reason to be interested, as dialysis is costly. In the Netherlands, 1% of the total healthcare budget is spent on patients with ESRD, who only constitute 0.0006% of the population.^26 27^ Furthermore, transplantation is associated with higher quality of life for patients with ESRD compared with dialysis treatment. It is therefore valuable, from both patient and societal perspective, to conduct a complete and extensive cost-effective analysis and consequently to follow-up those results in terms of policy.

### Quality assurance system

Protocol adherence may be of importance to guarantee the effects of the home-based education. First, we expect a positive relation of adherence with outcome in terms of communication, knowledge and the number of transplantations. Second, any problems or regrets of donors and/or patients can only be justified if the evidence-based protocol was followed. The protocol has also been developed after thorough ethical consideration (28), which justified all characteristics of the programme. It can therefore be argued that health insurance makes reimbursement indispensable of the degree of protocol adherence of healthcare suppliers. Moreover, they should facilitate the quality assurance system as an integral part of the programme and ensure that the quality of the interventions is independent of the healthcare suppliers.

### Limitations

Investigating the (cost-)effectiveness of the home-based educational programme has its limitations. In health economics modelling, there is always a trade-off between the feasibility and transparency of the cost-effectiveness model and the level of details of real-life conditions as represented in the model. The more details, the more the model resembles real life, but the downside is that data should be available at that same level of detail and that the model becomes too complex in its feasibility. An example is that we assume that the mortality on dialysis is the same in the second and following years on dialysis. Hence, we know from literature that the mortality chance changes, but the data in later years are scarce and again the model would become more complex, as more ‘tunnels states’ have to be introduced. We expect that this trade-off will be most prominent in the transition changes between health states. We expect less obvious trade-offs for costs and utility assessment, as we have sufficient data for those variables.

### Cooperation

This investigation is a cooperation between many parties, who all have expressed their support. Obviously, it is possible that this support can be withdrawn for several reasons. For instance, we depend on data from a large national database with records of patients with ESRD (*Nefrovisie*). Hence, much efforts are and will be put in preserving relationships and communication in order to maximise fair successful implementation chances for the programme.

### Ethical considerations

Another challenge that we face is the ethical consideration of promoting living kidney donation through a home-based intervention. Previous studies on the ethics of this argued that such promotion is justified only when the conditions are met, such as (1) participation must be completely voluntary throughout the intervention, (2) no undue pressure should be put on the participants, (3) the education is neutral and non-directive, and (4) the purpose and the procedure should be clear to all participants.^28 29^ That does not mean there are no negative consequences whatsoever, but it does mean that the positive outcomes outweigh the negative. It could well be that a patient and/or a donor may regret the decision to have undertaken a transplantation with a kidney of a living donor, and that the donor and/or patient, in hindsight, may have felt undue pressure to donate a kidney. Adherence to the protocol will minimise these potential negative effects. However, it is possible that regret or pressure could lead to negative publicity for the programme. That is a risk since such negative publicity could impede the chances of implementing the programme as standard care.^30^ Especially considering that deceased organ donation is currently subject to controversy in the Netherlands since the government and parliament have accepted a donor law. This law is an opt-out system entailing a positive ‘no-objection’ deceased donor organ donor registration as a default for all Dutch citizens.^31^ Given this potential harm due to negative publicity it is crucial to have (1) a protocol which is justifiable from a medical ethical perspective, (2) widespread support from the various organisations involved, and (3) a high quality in terms of protocol adherence and trained adequate educators. If these conditions are met, the quality of the process then justifies its outcome, which is a subtle trade-off between positive and negative outcomes.

### Implementation

Another challenge is the generalisability of the results of the previous effect study on home-based interventions done in Rotterdam. The RCT in the Rotterdam transplant area has shown that the home-based educational programme leads up to four times more LDKTs. The trial took place at the academic transplant centre (Erasmus Medical Centre in Rotterdam) where extensive efforts were already undertaken as part of the standard care to promote LDKTs.^3 32^ It is possible that in other transplant areas in the Netherlands, with less experience regarding promoting LDKT, effectiveness in terms of amount of LDKTs may differ. On one hand, this more cautious attitude may lead to lower results than in the Rotterdam transplant area. Hence, organisational conditions within those transplant centres may not optimally facilitate the favourable results of the interventions. On the other hand, if the number of LDKTs was lower than in the Rotterdam area, and the uptake of the intervention is high, the effect could even be higher than in the Rotterdam area. This is due to a higher effect potential in those centres where living donation was not promoted as actively.

### Learning curve

As with all new programmes, educators will inherently experience a learning curve during the first part of the implementation, which could influence the effectiveness of the programme. For instance, the goal of 50 patients per year per academic transplant centre and the goal of 20 patients per regional hospital may not be reached. Regular supervision (on-the-job) training and peer-to-peer coaching may help overcome this, but a learning curve is unavoidable.

### Policy implications

One of the main pillars of an efficient healthcare system is the ability to provide effective care to patients when needed. It is therefore necessary to have information on the effectiveness of the interventions and their cost to convince policymakers to reimburse the treatment. If the analysis confirms the effectiveness as well as the cost-effectiveness of the home-based educational programme, we recommend that this intervention should be part of standard care.

If the home-based educational interventions would become standard care, this could have several implications. First, it can be expected that patients who are unable to find a living donor will nevertheless profit from an increase number of living kidney donations, as the demand for deceased donor kidneys drops. In other words, the increase in living donation will further lower the waiting list for deceased donor donation as well and thereby increase the chance of a deceased donor donation for those patients without a living donor increases.

Second, the composition of the population of patients with ESRD may change. For instance, it can be expected that the proportion of patients on dialysis will drop and patients with a life-sustaining transplanted kidney will increase. This might have an influence on the demand for dialysis centres and the need for transplantation facilities. We, therefore, aim to incorporate this in a so-called dynamic model to estimate the prevalence over time. When modelling the prevalence, we could make estimates of the need for dialysis centres and transplantation facilities. However, modelling the facility is surrounded by uncertainty. For instance, dialysis centres may have financial incentives to fulfil dialysis capacity. If this would be the case, there will be no monetary benefits for society by increasing the transplant facilities if the proportion of dialysis capacity remains the same. This would mean that there will only be an increase in the average quality of life of patients with ESRD.

Finally, a cost-effectiveness analysis only might not be sufficient to set policy change in motion. Therefore, we anticipate that a policy recommendation accompanied with a BIA will also be required. A BIA addresses the expected changes in the expenditure of a healthcare system after the adoption of a new intervention. It can also be used for budget and resource planning.^33 34^

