**Methods and design:**

Patients with ESRD who do not have a living kidney donor are eligible to receive the home-based educational intervention. This is carried out by allied health transplantation professionals and psychologists across eight hospitals in the Netherlands. The cost-effectiveness analysis will be conducted with a Markov model. Cost data will be obtained from the literature. We will obtain the quality of life data from the patients who participate in the educational programme. Questionnaires on knowledge and communication will be used to measure the outcomes of the programme. Data on LDKT activities will be obtained from medical records up to 24 months after the education. A protocol adherence measure will be assessed by a third party by means of a telephone interview with the patients and the invitees.

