**Trial registration number:**

NL6529

Strengths and limitations of this studyWorking with a state-transition model involves a trade-off between feasibility and transparency of the model and the level of details of real life conditions.We do not have a control group in the implementation study, we will use the reported effectiveness of a randomised controlled trial conducted previously.By making a dynamic state-transition model, we can model the prevalence and incidence of patients with end-stage renal disease, and consequently the capacity for the facility needs which has not been done before.We have high-quality data at our disposal.

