Effects (QALYs)	EQ-5D-5L is conducted prior to the intervention and 6, 12 and 24 months after the intervention.
Transition probabilities Between treatment modalities Mortality rate	Estimated from the database of Nefrovisie
Incidence rates	Estimated from the database of Nefrovisie
Effect size of the intervention	Used from previous studies^3 4^

EQ-5D-5L, 5-level version of EuroQol-5 Dimension; QALY, quality-adjusted life years; RRT, renal replacement therapy.

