#### Model description

A simplified graphical representation of the Markov model showing only the treatment categories, rather than all the individual Markov states is represented in figure 1. Patients continuously enter the model (inflow) at the start of the cycle and can start on haemodialysis, peritoneal dialysis or transplantation. From there they can move between these treatment modalities. Diabetics and non-diabetics are modelled separately since the transition probabilities between the treatment modalities differ between these groups. Since the incidence of kidney failure is increasing, we will also model this in the cost-effectiveness analysis. This will be calculated using data from the database of *Nefrovisie*, a large national database with records of patients with ESRD. As stated before, the model will include probabilistic sensitivity analysis using Monte Carlo simulation. This means that mean numbers of patients per year per treatment modality will be modelled, and the uncertainty surrounding those mean numbers of patients (ie, 95% CIs). Transition probabilities and incidence rates will be based on primary data and will include uncertainty. Costs and utilities will be included in the model as distributions rather than point estimates.

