#### Outcomes

The outcome of the implementation will be compared with the baseline situation; the situation before this programme was implemented. The effect size, in terms of an increase in LDKT, will be used from the RCT conducted earlier. Through sensitivity analyses an estimation can be made of the cost-effectiveness of the intervention whether this assumption is either an underestimation or overestimation. A critical assumption will be the extrapolation of the effects after the 2 years.

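### The recommendation requires the analysis to confirm effectiveness, but the transplant effect is an imported input, so only cost-effectiveness conditional on that effect can be shown

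*Protocol article*

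**What the plan says.** All references are to the Protocol article.

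- **Policy implications (Discussion).** The programme is recommended as standard care on this condition: "If the analysis confirms the effectiveness as well as the cost-effectiveness of the home-based educational programme".
- **Strengths and limitations box.** "We do not have a control group in the implementation study, we will use the reported effectiveness of a randomised controlled trial conducted previously".
- **Outcomes.** "The effect size, in terms of an increase in LDKT, will be used from the RCT conducted earlier". The section calls this an assumption and plans sensitivity analyses in case it is too low or too high.
- **Table 1 (Markov model).** The effect size is listed as a parameter with the source "Used from previous studies", citing both the RCT and the cross-over study. Transitions between modalities come from the national registry.
- **Markov model.** Costs and effects per health state are not altered by the intervention. Apart from programme costs, it acts only by changing transition probabilities. Every parameter is to carry a probability distribution.
- **Abstract, Methods and design.** "Data on LDKT activities will be obtained from medical records up to 24 months after the education".
- **Introduction and Quality assurance.** The stated use of those LDKT data is their relation to protocol adherence.
- **Implementation (Discussion).** Outside Rotterdam, "effectiveness in terms of amount of LDKTs may differ", in either direction.

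**The concern.** An analysis can confirm only what its data could have contradicted. Here the LDKT effect goes into the model as an assumption, and every health gain credited to the programme follows from it. The study will record LDKTs in eight hospitals for up to 24 months, but no described step compares those counts with the assumed effect or revises it.

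The article itself says the effect may not carry over to other centres. If it did not, the effect input would be the same. A favourable result could then be read by the Dutch National Health Care Institute and the insurers as evidence that the programme raised LDKT in the wider roll-out, when that had been assumed.

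**Working it through.** **1. What each statement allows.**

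- Benefit enters the model only through changed transition probabilities (Markov model).
- The size of that change comes from earlier work (Outcomes; Table 1).
- No concurrent comparison exists in the study (Strengths and limitations box).
- The study's LDKT counts are related to adherence among educated patients (Quality assurance), which gives no contrast with patients who were not educated.

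It follows that the model returns cost-effectiveness given the imported effect and cannot test that effect. The Outcomes section does open by saying that the implementation will be compared with the situation before the programme. Its next sentence supplies that contrast from the RCT, and the Markov model section describes baseline and post-implementation as two model situations.

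**2. Reproducing the imported result.** Inputs from the Introduction: 17 versus 4 LDKTs, 163 patients on dialysis, p=0.003. Arm sizes are not given; 82 and 81 are assumed.

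- Pearson chi-square without continuity correction: p = 0.0026, which rounds to the stated 0.003.
- Ratio of counts: 17/4 = 4.25, in line with the fourfold claim.

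**3. Its precision.**

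- Risks: 17/82 = 20.7%; 4/81 = 4.9%.
- Risk ratio: 0.2073/0.0494 = 4.20. SE of the log ratio = √(1/17 − 1/82 + 1/4 − 1/81) = 0.533. 95% CI: 4.20 × exp(±1.96 × 0.533) = 1.48 to 11.94.
- Risk difference: 0.2073 − 0.0494 = 0.158. SE = √(0.2073 × 0.7927/82 + 0.0494 × 0.9506/81) = 0.0508. 95% CI: 0.058 to 0.258.
- Patients educated per extra LDKT: 1/0.158 = 6.3, with limits 1/0.258 = 3.9 and 1/0.058 = 17.
- Splits from 84/79 to 79/84 move the risk ratio only from 4.0 to 4.5, so the assumed arm sizes matter little.

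**4. Whom the estimate covers.** The RCT enrolled patients on dialysis. The regional hospitals target patients who have not yet started RRT, and the university hospitals take both groups. For patients before RRT the article reports 34 LDKTs among all 80 cross-over participants (42.5%). The control group was also educated in the second phase, and no LDKT contrast between arms is given.

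**5. What the study's own LDKT rate could and could not show.** Planned recruitment is 4 × 50 × 2 + 4 × 20 × 2 = 560 if the regional figure of 20 is per year, or 4 × 50 × 2 + 4 × 20 = 480 if it is a total per hospital. Suppose, for illustration, that 20.7% of educated patients have an LDKT. The no-programme rates below are assumptions; the first equals the RCT control risk.

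| Assumed no-programme rate | Implied risk ratio | Extra LDKTs of 560 | Extra LDKTs of 480 |
|---|---|---|---|
| 4.9% | 4.2 | 88 | 76 |
| 10% | 2.1 | 60 | 52 |
| 15% | 1.4 | 32 | 28 |
| 20.7% | 1.0 | 0 | 0 |

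The same observed rate fits a fourfold effect or none. It can show whether the model's predicted LDKTs occurred and it can bound the effect under stated assumptions, but alone it does not identify the effect.

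**The case against.** The best defence is that nothing is hidden. The article discloses the missing control group and the borrowed effect, calls the effect an assumption, plans sensitivity analyses in both directions and discusses transferability. A randomised estimate is a sound base case, better than an uncontrolled before-and-after change. The sentence in Policy implications is a remark in the Discussion, not a prespecified decision rule, and none of the stated hypotheses is a controlled test of LDKT effectiveness. The LDKT data are absent from Table 1 because they serve the adherence objective.

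Most of this stands, and it limits the point to what may be concluded. It does not rescue the wording. Sensitivity analyses show how far the result depends on the effect; they do not confirm it.

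A reader might also infer more than the documents support:

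- **That the effect lies outside the probabilistic analysis, so the 95% intervals are too narrow.** Model description says "Costs and utilities will be included in the model as distributions rather than point estimates" and does not name the effect size, and Outcomes treats it as an assumption to vary. But the Markov model section gives each parameter a distribution, and Table 1 lists the effect as a parameter. Narrow intervals are conjecture.
- **That no study data could overturn the conclusion.** Intervention costs, EQ-5D-5L utilities and work status come from the study and can change the cost-effectiveness result. Only the LDKT effect is external.
- **That the effect is the most influential input.** No comparison of inputs is available, and the article itself calls extrapolation beyond 2 years critical.

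**Conclusion.** The point holds as a limit on inference. As described, the analysis can establish cost-effectiveness conditional on the earlier effect; it cannot confirm effectiveness in the eight hospitals, which is half of the condition for the recommendation. The imported effect is compatible with a risk ratio from about 1.5 to about 12 and a risk difference from about 6 to about 26 points. The programme cost per extra LDKT could therefore differ by a factor of about 4.4 (0.258/0.058) between the limits.

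This rests on near-equal RCT arms and on the article's explicit statements of where the effect comes from. No text forbids a later check against the study's own LDKTs; none is described. The article also names the RCT alone in Outcomes but both earlier studies in Table 1.

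**What to change.** 1. Reword the condition in Policy implications so that the recommendation rests on cost-effectiveness given the effect seen in the earlier trial.
2. Compare model-predicted with observed 24-month LDKTs among educated patients in the eight hospitals, separately for patients on dialysis and patients not yet on RRT. Use the observed rates, with stated no-programme rates, to set the lower and upper effect values in the planned sensitivity analyses. Label this as non-randomised.
3. Reconcile Outcomes with Table 1 on the source of the effect, and confirm in one sentence that the rule of a distribution for each parameter covers the effect size.

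The cost is a little more analysis, on LDKT data already being collected, and a less favourable claim. A comparison with pre-programme or registry rates would be a useful addition if comparable patients (consenting, eligible, without a living donor) can be identified. The article does not show that they can, and the comparison would be confounded, so it should stay optional and not be a condition for the recommendation.

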## Conclusion

If our hypotheses are confirmed, we hope by presenting an extensive cost-effectiveness analysis, a BIA, and a policy recommendation that policy change will be set in motion, which again would benefit both patients with ESRD and society.
